### Study population

2.3

Inclusion and exclusion criteria for participants are shown in Table 3, Table 4. Participants will be asked not to change or interrupt their existing physiotherapy or pharmacotherapy, e.g. their treatment as usual, during the data acquisition timeline. Written informed consent from participants will be obtained by a scientific study team.

**Table 3 tbl3:** Requirement profile participant inclusion.

Inclusion criteria
Confirmed multiple sclerosis with spasticity of the lower limbs (all phenotypes)
Expanded Disability Status Scale (EDSS) score between 4 and 6
Written informed consent of the patient
Consent of the study site physician
Legal competency
Minimum age of 18 years

**Table 4 tbl4:** Requirement profile participant exclusion.

Exclusion criteria
Hippotherapy within the last 12 months
Parallel participation in other intervention studies
Persons, who are in a dependent/employment relationship with the sponsor or investigator (potential conflict of interest)
Body weight over 90 kg
Acute exacerbation of the disease four weeks before the start of therapy
No balance while sitting
Planned start of treatment with new antispastic medication or with medication that may have an influence on test parameters (examples: Nabiximols (Sativex®), neuraxial administration of baclofen; 4-aminopyridine)
Seizure disorder not controlled by medication
No or insufficient ability to spread the legs so that the patient can sit on the horse
Known severe osteoporosis
Known severe osteoarthritis of the hip
Known severe scoliosis that could be aggravated by hippotherapy
Severe blood clotting disorders where there is a risk of hematoma due to hippotherapy
Insufficiently stable concomitant diseases in the field of internal medicine, gynecology and/or surgery
Allergy to horse hair
Pregnancy
No balance impairment (Berg Balance Scale over 50 points before the start of the intervention)

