### Design

2.1

A randomized controlled trial design will be applied to obtain data from in total 140 subjects: (1) hippotherapy intervention group (IG) (approx. N = 70) and (2) control group (CG) (approx. N = 70). Within a project duration of two years and six months (01.01. 2024–30.06. 2026), both groups, IG and CG, are to be assessed during two separate study cycles with IG (N = 35) and CG (N = 35) in each study cycle. Each study cycle will consist of a twelve-week intervention period (1x hippotherapy/week) with a pre/post measurement and a six-week follow-up measurement (see Fig. 1). Before therapy begins, the population will be randomly and evenly assigned to one of two groups: IG or CG.

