### Intervention

2.4

Hippotherapy will be carried out once a week for 30 min additionally to patients‘ usual physio- and/or pharmacotherapy (1-2x/week). The vibrations of the horse's back and the rhythm of the horse's stride are being utilized to achieve physiological reactions to improve individual balance performance, mobility, muscle strength and an upright sitting position. It will be carried out as a complementary movement-therapeutic approach for study-related purposes and not part of the treatment routine of patients with MS in standard outpatient rehabilitation. Therapies are standardized according to the principles of DKThR and carried out by trained physiotherapists plus state-approved hippotherapy (DKThR)® license [8]. The Intervention manual for hippotherapy (DKThR)® can be found in Appendix A1. The CG will undergo their treatment as usual without additional hippotherapy. Treatment as usual is defined as the continuation of physiotherapy (1-2x/week) and/or pharmacotherapy. The physiotherapeutic treatment aims to improve individual mobility, build up reduced muscle strength, stretch shortened muscles and loosen tense muscles, as well as alleviate pain through massages and/or heat/cold/electrotherapy. This is supplemented by gait and mobility training (everyday mobility) as well as weight-bearing training, improved coordination and balance and stabilization training. The CG will be offered 5 hippotherapy sessions (30-min units once a week) as an incentive after completing the study and to ensure compliance with regard to ethical aspects. Changing inclusion and exclusion parameters will lead to a drop out. A change in medication or participation in another measure (e.g. study, rehabilitation activity) is not permitted during the trial. Participation in less than 9 out of 12 hippotherapy sessions will lead to a drop out. Pregnancy in participants will also lead to a drop out.

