### Screening and randomization

2.6

Participant recruitment will take place using a flyer in local media, at the study sites and at the supporting partner organization, German Multiple Sclerosis Society (DMSG) (Hannover, Germany). Subsequently, interested candidates can contact the scientific study team via telephone or email. An initial telephone interview will be conducted using a standardized script, where eligibility is checked according to the inclusion and exclusion criteria. Inclusion and exclusion criteria are similar to the criteria in the MS-HIPPO study and can be seen in Table 3, Table 4 [14]. If an inclusion is possible, patients will subsequently be referred to a study site physician, who will carry out an initial examination and approve a medical clearance. The patients included, will be informed about the study protocol and asked for their written consent. Patients can withdraw from the study at any time; medically relevant withdrawals are forwarded to the monitor and responsible ethics committee. After initial contact, written informed consent and medical clearance of the participants, they will be randomly assigned to IG and CG. The allocation sequence will be generated by computer-generated random numbers. Individuals are randomized stratified by location, gender distribution of the disease and Expanded Disability Status Scale (EDSS) [34]. A code-generated random mechanism will be used for concealment. Scientific study personnel will generate the allocation sequence, enroll participants, and assign participants to interventions based on a stratified adaptive randomization.

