### Assessment

2.7

At baseline, post and follow-up, balance performance, BBS, EEG, quality of life, fatigue, pain, spasticity and activity- and participation-related parameters will be collected. The following table (Table 7) shows the time schedule of patient enrolment and intervention.

**Table 7 tbl7:** Time schedule.

	Registration	Baseline assessment	Post assessment	Follow-up assessment
Fulfillment of the inclusion criteria	X	12 weeks hippotherapy or 12 weeks treatment as usual		6 weeks treatment as usual
Written declaration of informed consent	X			
Medical clearance	X			
Assignment to the study group	X			
Anthropometric data	X			
Balance assessment/EEG		X	X	X
BBS		X	X	X
Quality of life (MSQoL-54)		X	X	X
Fatigue (FSS)		X	X	X
Pain (VAS)		X	X	X
Spasticity (NRS)		X	X	X
WHODAS 2.0 36-Self		X	X	X
EQUITEDO® (IG only)		X	X	

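### The relapse exclusion is timed from a date that falls after randomisation and is not defined for controls, so it can remove randomised patients and could be applied differently by arm

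*Protocol article*

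**What the plan says.** Table 4 in section 2.3 lists as an exclusion "Acute exacerbation of the disease four weeks before the start of therapy".

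Four other parts of the article bear on how that criterion works:

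- **Order of events.** Section 2.1 states "Before therapy begins, the population will be randomly and evenly assigned to one of two groups: IG or CG". Section 2.6 puts assignment after consent and clearance: "After initial contact, written informed consent and medical clearance of the participants, they will be randomly assigned to IG and CG". Table 7 places assignment in the registration column and the first Berg Balance Scale (BBS) measurement in the later baseline column.
- **Control arm.** Section 2.4 states "The CG will undergo their treatment as usual without additional hippotherapy" and adds "Treatment as usual is defined as the continuation of physiotherapy (1-2x/week) and/or pharmacotherapy". Table 7 gives the period after baseline as "12 weeks hippotherapy or 12 weeks treatment as usual".
- **Eligibility before and after enrolment.** Section 2.6 describes a telephone interview "where eligibility is checked according to the inclusion and exclusion criteria", followed by a physician's examination. Section 2.4 then states "Changing inclusion and exclusion parameters will lead to a drop out".
- **Analysis sets.** Section 2.8 defines the primary mITT set as registered patients with a completed pre-measurement. The per-protocol (PP) set, used for sensitivity analysis, requires completion with no more than very minor violations.

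**The concern.** An eligibility criterion should be decidable before allocation, from information that exists in the same form for both arms. This one is not. Its reference date is still in the future when the patient is screened and randomised, and it is worded for a treatment that only one arm begins.

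A recent relapse plausibly affects balance, which is the primary endpoint. If relapse can lead to removal after assignment, and if sites must decide for themselves which date applies to a control, the arms may come to differ in recent disease activity. Patients and therapists know the allocation, so that decision would not be made blind. The direction of any resulting bias cannot be predicted: a relapsed patient who is kept may recover or decline over the following weeks.

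**Working it through.** The article gives no figure to reproduce here. It states neither a relapse rate nor the interval from assignment to first session. The check is of the text, followed by a bound on size.

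**1. Where the window ends.** Sections 2.1 and 2.6 and Table 7 give the order: clearance and consent, assignment, baseline, 12-week period. The start of therapy is therefore later than assignment. Any part of the four weeks that lies between assignment and the first session cannot be checked at screening.

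**2. What date a control has.** Under section 2.4 a control continues existing care, so no therapy starts. Table 7 gives controls a parallel 12-week period, whose first day is a natural substitute. The article does not say that this day serves as the reference date for the criterion.

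**3. What follows from a relapse in the window.** The drop-out rule in section 2.4 can turn a newly met exclusion criterion into a drop-out. The effect depends on when the relapse occurs:

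| Relapse occurs | mITT set as defined | Other exposure |
|---|---|---|
| Between assignment and baseline | A patient dropped here has no pre-measurement and leaves the primary set | Also lost to PP |
| Between baseline and first session | Stays in mITT | May lack a post-treatment BBS for the primary ANCOVA; may leave PP |

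Mixed models that use all available measurements are planned, but as a sensitivity analysis to the ANCOVA.

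**4. Size.** Inputs: about 70 patients per arm (section 2.1), a four-week window (Table 4), and assumed rates of 0.2, 0.3 and 0.5 relapses per patient-year. Expected relapses in the window per arm = 70 × rate × 4/52:

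- 70 × 0.2 × 4/52 = 1.1
- 70 × 0.3 × 4/52 = 1.6
- 70 × 0.5 × 4/52 = 2.7

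These are upper figures at each rate. They assume that the whole window falls after assignment and that every such relapse leads to drop-out. For the mITT set, only the part of the window between assignment and baseline counts, so the number is smaller.

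**The case against.** A reader might infer that the same relapse removes a hippotherapy patient and leaves a control in the trial. The documents do not support that. Section 2.1 speaks of one 12-week intervention period per study cycle and uses the start of therapy as a time point for the whole population. Table 7 shows the two arms in parallel, so a matching start for controls is the natural reading. The drop-out rule names no arm. Table 7 marks fulfilment of the criteria at registration only, and no eligibility re-check before the first session is scheduled. One-arm exclusion is a possible result of a strictly literal reading; it is not something the plan prescribes.

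A reader might also scale the number affected by the whole wait from assignment to first session. At 0.5 relapses per year and an assumed 12 weeks this gives 70 × 0.5 × 12/52 = 8.1. But a relapse more than four weeks before therapy does not meet the criterion, so the four-week figures are the right bound. The article also gives no basis for a long wait; running two cycles does not imply one.

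Finally, the mITT definition protects the primary set from exclusions after baseline. That is correct and limits the harm considerably. It does not cover the gap between assignment and baseline, and membership of the set does not supply a missing post-treatment BBS.

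What remains is that screening before randomisation cannot settle a criterion whose reference date comes later, and that the article keeps the criteria in force after enrolment.

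**Conclusion.** The point holds as a badly fixed time anchor. The relapse criterion ends on a date after randomisation, has no stated equivalent for controls, and can act as a drop-out rule on patients already assigned. That leaves room for prognosis-related exclusion that could differ by arm; it does not show that such exclusion will occur.

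The exposure is the gap between assignment and baseline for the primary set, plus the PP set and missing post-treatment BBS values. At assumed rates of 0.2 to 0.5 relapses per patient-year it is at most about 1 to 3 of 70 patients per arm, with the direction of bias unknown. This is a minor to moderate wording issue, worth correcting because the correction is nearly free.

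**What to change.** - In Table 4, keep the four-week length but, for trial eligibility, assess it against a date before allocation that both arms share: randomisation or medical clearance. The baseline assessment would serve only if it were moved ahead of assignment, because Table 7 now places it afterwards.
- State that an exacerbation after that date is recorded identically in both arms, does not make a randomised patient ineligible, and does not remove the patient from the primary analysis set or from outcome assessment.
- Reconcile the drop-out rule in section 2.4 with this statement, so that a change in eligibility after assignment does not end follow-up.

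Whether sessions go ahead after a relapse is a separate clinical decision, which this change leaves untouched.

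The cost is a short change of wording in two places. The downside is that a few patients with a recent relapse have their randomisation deferred.

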### Intervention

2.4

Hippotherapy will be carried out once a week for 30 min additionally to patients‘ usual physio- and/or pharmacotherapy (1-2x/week). The vibrations of the horse's back and the rhythm of the horse's stride are being utilized to achieve physiological reactions to improve individual balance performance, mobility, muscle strength and an upright sitting position. It will be carried out as a complementary movement-therapeutic approach for study-related purposes and not part of the treatment routine of patients with MS in standard outpatient rehabilitation. Therapies are standardized according to the principles of DKThR and carried out by trained physiotherapists plus state-approved hippotherapy (DKThR)® license [8]. The Intervention manual for hippotherapy (DKThR)® can be found in Appendix A1. The CG will undergo their treatment as usual without additional hippotherapy. Treatment as usual is defined as the continuation of physiotherapy (1-2x/week) and/or pharmacotherapy. The physiotherapeutic treatment aims to improve individual mobility, build up reduced muscle strength, stretch shortened muscles and loosen tense muscles, as well as alleviate pain through massages and/or heat/cold/electrotherapy. This is supplemented by gait and mobility training (everyday mobility) as well as weight-bearing training, improved coordination and balance and stabilization training. The CG will be offered 5 hippotherapy sessions (30-min units once a week) as an incentive after completing the study and to ensure compliance with regard to ethical aspects. Changing inclusion and exclusion parameters will lead to a drop out. A change in medication or participation in another measure (e.g. study, rehabilitation activity) is not permitted during the trial. Participation in less than 9 out of 12 hippotherapy sessions will lead to a drop out. Pregnancy in participants will also lead to a drop out.

### Outcomes

2.5

The primary endpoint of the study is the change in balance performance after 12 units of hippotherapy (change from baseline). To assess the primary outcome measure, the Berg Balance Scale (BBS) will be used in an independent assessment by a blinded observer (Table 5). Blinded assessors will be trained for collecting the BBS data prior to the start of the intervention by the investigators. Unblinding is not permitted during the trial. Assessors will be trained to collect EEG, force plate and Posturomed® data. Therapists at study centers will be educated and instructed on how to complete Adverse Event Report forms (AEs) and EQUITEDO® assessments.

**Table 5 tbl5:** Protocol Berg Balance Scale.

(0–4 points/sum score)
1. from sitting to standing
2. standing without support
3. sitting without support
4. from standing to sitting
5. transfers
6. standing with eyes closed
7. standing with feet close together (close foot stance)
8. reaching/longing forward with outstretched arm
9. picking up an object from the floor
10. turn around to look backwards
11. turn 360°
12. alternately place your feet on a footrest
13. standing with one foot in front of the other (tandem stand)
14. standing on one leg (one-legged stand)

As the gold standard for measuring balance in a clinical setting, the BBS enables the results of this therapy to be compared with other interventions, and is therefore applied as primary outcome measure [18,19]. In regard to validity and reliability, the BBS shows satisfactory values [[18], [19]].

Additional to BBS, a balance task and a balance perturbation task will be implemented. The balance task will be performed on a force plate (AccuGait-Optimized (ACG-O), Advanced Mechanical Technology, Inc., Massachusetts, US). The task consists of: standing with eyes open and closed, closed stance, (semi-) tandem stance and (semi-) one-legged stance (Table 6). As the participant sways while standing on the force plate, the center of pressure (CoP) excursion in millimeters in all directions of sway (anterior–posterior and medial–lateral) will be measured with regard to the attainment of postural stability. In addition, brain activity will be recorded by means of electroencephalography (EEG) using a portable system with 32 electrodes (LiveAmp, Brain Products GmbH, Gilching, Germany). By measuring the excitatory postsynaptic action potentials, a movement-induced change in brain activity in the theta, alpha-1 and alpha-2 frequency bands is expected.

**Table 6 tbl6:** Balance and balance perturbation task.

Protocol balance tasks (sequence of tests 5–7 randomized)
1. sitting - eyes open - 120s
2. sitting - eyes closed - 120s
3. standing - eyes open - 3x (20s–20s break) - 45s break
4. standing - eyes closed - 3x (20s–20s break) - 45s break
5. standing, feet close together - 3x (20s–20s break) - 45s break
6. (semi-) tandem stand (feet behind each other) - 3x (20s–20s break) - 45s break
7. (semi) one-leg stand - 3x (20s–20s break) - 45s break break 5 min
8. 10 Perturbations Posturomed® - (30s–45s break) 2nd break 5 min.
9. 10 Perturbations Posturomed® - (30s–45s break)

Duration balance task: 12 min 30s; duration balance perturbation task: approx. 30 min.

The balance perturbation task will be performed on an oscillating sensorimotor therapy device (Bioswing Posturomed®, Haider, Pullenreuth, Germany) [20]. The task consists of reactive balance control after a previous balance perturbation (with manual triggering of the oscillating movements (see Table 6)). The oscillating mechanism enables dosed, damped pendulum movements with standardized oscillation amplitudes and frequencies (perturbations) [20]. The stabilization behavior is recorded by an acceleration sensor (3D Acceleration Sensor, Brain Products GmbH, Gilching, Germany). With regard to the attainment of postural stability, the postural corrective information from the start of movement of the platform, shall be calculated via the accelerometer data. During the balance perturbation task, perturbation-evoked cortical potentials will also be recorded via EEG.

In regard to technical specifications, the AccuGait-Optimized force plate (Advanced Mechanical Technology, Inc., Massachusetts, US), provides a measuring accuracy of .01 % according to the manufacturer, and is CE-certified [21]. Based on precision grid calibration technology, measurement accuracy is secured (10 separate force values for 400 locations on the platform surface) [21]. AMTI Balance Clinic measurement software will be used for data processing (Advanced Mechanical Technology, Inc., Massachusetts, US version, 1.5.0). Measures of CoP (average, range, standard deviation, path length, 95th percentile ellipse measure, velocity) will be calculated. The sampling rate will be 50 data sets per second, filtered with a fixed 100 Hz third-order analog filter. Three valid trials per condition will be collected, which is consistent with current methodological practice to maximize the reliability of CoP-based balance measures in neurological populations and minimize the risk for distort CoP outcomes due to fatigue [[22], [23], [24], [25]]. The number and duration of tasks and trials are specified in Table 6. The EEG system LiveAmp 32 and actiCAP slim/snap (Brain Products GmbH, Gilching, Germany) fulfills the requirements of Medical Device Directive 93/42/EEC (MDD), classification DIN EN 62304, class 1 [26]. Bioswing Posturomed® diagnostic device (Haider, Pullenreuth, Germany) is certified according to MDR 2017/745 class I medical device [20].

The secondary endpoints of the study will be the measurement of fatigue using the Fatigue Severity Scale (FSS) [27]. The FSS represents the gold standard for measuring fatigue [28]. In addition, the Multiple Sclerosis Quality of Life-54 Questionnaire is used as a disease-specific instrument (MSQoL-54), which supplements the SF-36 questionnaire for recording health-related quality of life with 18 MS-specific items [29]. The MSQoL-54 is a validated and established instrument in measuring quality of life in MS [29]. Pain will be measured using the visual analog scale (VAS) [30]. VAS is used because it represents a simple and frequently used method for measuring pain in clinical practice and is also regarded as a measure of the effectiveness of treatment and thus offers comparability to other studies [30]. Change in spasticity will be measured via Numeric Rating Scale (NRS) [31]. NRS is a validated and established instrument for the measurement of spasticity [31]. The self-assessment version of the ICF-based WHO Disability Assessment Schedule 2.0 (WHODAS 2.0) will be used to measure activity- and participation-related parameters [32]. WHODAS 2.0 is validated and links back to ICF domains [32]. In addition, an ICF-based EQUITEDO® assessment to be completed by the therapists as an external assessment will be used to document the process and results of the hippotherapy measures [33]. EQUITEDO® assessment is also validated and also linkable to ICF domains [33]. Furthermore, a self-constructed questionnaire for monitoring regularity, frequency, and content of the treatment as usual of both IG and CG across the full duration of the intervention (including follow-up) will be applied. Questionnaires will be filled out and processed digitally using two software programs Questback Unipark (Tivian XI Ltd., Cologne, Germany) and EQUITEDO® application (Research Institute for Inclusion through Physical Activity and Sports Ltd., Frechen, Germany).

